### Data analysis (t_2_ in Fig. 1)

The pooled routine dataset is sent from AOK to the aQua institute. The aQua institute selects, filters and anonymizes the data. Lastly, the aQua institute delivers the anonymized patient dataset to the Institute for Clinical Epidemiology and Applied Biometry (IKEaB) for statistical analysis. All of these transfers use a secure, encrypted protocol and are authenticated. The relevant data sources are subject to extensive quality management processes. To secure data protection of interview and questionnaire data as well as process data from the KSYOS system, the Tübingen University Hospital’s (UKT) data protection agency is involved. They are independent from the sponsor.

For the primary outcome, Poisson regression is chosen as an analysis tool. To consider practice size and patient load, the number of practice KV bills during the intervention phase is applied as an offset. The dichotomous factor “study arm” is applied for the calculation. The GPs are the unit of observation. For both study arms, separate confidence intervals are created for the number of referrals per KV bill.

For the sample size calculation, a simple *t* test was used. In contrast to the sample size calculation, the statistical analysis will use a more complex method (Poisson regression). This is expected to lead to an increased power of the study, because the offset “total number of KV bills during intervention” explains parts of the variability between GP teams. Study power should thus be over 80%. Primary analysis will be calculated as a Poisson regression with a significance level of 5% (two-sided). Analogous methods will be applied to secondary outcomes (see later). However, the interpretation of local significances is not designed to be strictly confirmatory. Due to the multitude of secondary parameters lacking hierarchical structure, a correction for multiple tests is unrealistic. Descriptive analyses are performed following scaling and observed data distribution.

Secondary outcomes are analyzed using adequate regression models (linear, ordinal, logistic, multinominal) and considering cluster effects. The generalized estimating equations (GEE) method is employed. For GP team-related analyses (unit of observation = GP), appropriate regression models without cluster adjustment are used, because the outcome is only measured once per GP team. This is especially true for analyses based on KSYOS data (process data) and AOK insurance data. The same applies for secondary endpoint analyses among dermatologists, GPs and nonphysician staff. Questionnaires will be piloted using the “think aloud” method [30]. During the pilot, some participants (patients and care providers) are asked to read questionnaire items and voice their thoughts on them. A research team member observes the participants and creates a protocol. The protocols of these observations are then used to improve the questionnaire.

Interviews are transcribed and then analyzed using qualitative content analysis [31]. Analysis will continue until thematic saturation is reached. The resulting category system will provide information additional to the questionnaire data and help understand patients’ and care providers’ perspectives on teledermatology.

Ancillary studies may include analysis of anonymized process data and/or anonymized pictures of lesions. Design and planning will be presented in separate publications.

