**Fig. 1 Fig1:**
[figure not shown]
SPIRIT 2013 figure with schedule of enrolment, interventions and assessments. GP general practitioner, HzV Hausarztzentrierte Versorgung

This project is one of the first to be supported by the Federal Joint Committee’s Innovation Fund. In order to facilitate innovations in German health care, the fund was created in 2015 with the “Law on Strengthening Statutory Health Care” (Gesetzliche Krankenversicherungs-Versorgungsstärkungsgesetz) [23]. The Federal Joint Committee call for proposals is competitive and uses external peer review. The sponsor has no influence over study design; collection, management, analysis and interpretation of data; writing of the report; and the decision to submit the report for publication. Neither does the sponsor have ultimate authority over any of these actions.

To describe the study setting, a short overview of the health insurance system in Germany is presented. There are around 116 statutory health insurance companies in Germany. The Allgemeine Ortskrankenkasse (AOK) is one of the largest statutory health insurance funds with over 25 million insured persons (35% of all statutory insured persons) [24]. Statutory insurance companies are self-governed corporations under public law. The state of Germany or federal regions may be shareholders in these companies. They must provide health services for everyone who is insured. They also must accept every applicant for health services. Private health insurance companies, on the other hand, are basically privately owned.

In addition to their regular coverage, all health insurance companies may sign direct contracts with GP representatives and other specialist physician groups. An example of such a contract is the Hausarztzentrierte Versorgung (HzV) (GP-centered health care). Patients enrolled in the HzV decide to enlist to one GP. Every primary care physician has regular contracts with the Association of Statutory Health Insurance Physicians (KV). This association negotiates outpatient treatment costs with the legislator and the insurance companies. Within the regular contracts, the primary physician is remunerated per consultation and treatment. In the case of GP-centred care, the GP receives an additional amount per capita directly from the insurance company.

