### Outcomes

The primary outcome measure is the number of conventional referrals from GPs to dermatologists.

Secondary endpoints will be evaluated using a mixed-methods approach. This will allow us to evaluate different aspects of the implementation process. For instance, the teledermatology system will provide information about the referral time and process quality. This data source is complemented by questionnaire surveys from all participating groups. Both care providers (GPs, dermatologists, GP practice staff) and patients (teleconsultation patients and patients who have declined a teleconsultations) will receive questionnaires on acceptance and feasibility. Patient questionnaires will also include all items from the Dermatology Life Quality Index (DLQI) [27]. Semi-structured face-to-face interviews (*n* = 15 patients who have received a teledermatology referral and n = 15 care providers, such as GPs, dermatologists and GP practice staff) will provide additional information to the surveys. Lastly, a health economics analysis based on routine data and support costs for the implementation of the teledermatology system is planned. Study sites (GP practices) will be visited once during the intervention phase by a study nurse for audit.

Details about the outcome parameters are presented in Table 2.

**Table 2 Tab2:** Primary and secondary endpoints, data sources and evaluation methods

Secondary endpoints (intervention group)					Primary endpoint (both groups)
Patients	GPs	Dermatologists	GP team staff	Teledermatology software/KSYOS (process evaluation)	Routine data
Care provider/customer satisfaction, description of technical processes with their advantages and disadvantages				• Number of teleconsultations • Time until dermatologist answers • Number of physical referral recommendations • Number of queries by dermatologists after teleconsultation • Type of disease treated by teleconsultation • Duration of complete teleconsultation process • Result of dermatologic consultation	• Number of referrals to dermatologists by GPs • Ambulatory dermatologic diagnoses • Ambulatory patient contacts with GPs and/or dermatologists due to skin conditions (including EBM^a^ keys) • Number of clinic referrals due to skin conditions
• Quality of life (DLQI, questionnaire) • Satisfaction with dermatologic care/telemedicine (questionnaire, interviews)	Appraisal of feasibility, practicability and barriers for implementation (interviews)				

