### Sample size calculation

The main scientific hypothesis is that the possibility of teledermatology in general practice will reduce the number of referrals to a dermatologist by 15% in the intervention group. The statistical null hypothesis is a reduction of 0%, the alternative is a reduction > 0%. The basis of the sample size calculation is an assumed reduction of 15%.

A mean of 120 referrals to dermatologists per year and GP is assumed. In 2015, 40% of AOK-insured patients were enrolled in the HzV [28, 29]. Thus, for the subgroup of AOK patients, 48 dermatological referrals per year and GP practice are to be expected in the control population during the 1-year intervention phase of the study. A Poisson distribution of the referrals for each GP team is assumed. Furthermore, a type I error of 5% (two-sided) and a type II error of 20% are defined. These assumptions lead to a calculation of 36 analyzable GP teams (with, on average, 48 referrals per year and GP practice each) per study arm. On the patient level, this amounts to 1728 patients with the indication for a referral to a dermatologist in total. A 15% reduction equals 260 referrals in total. A 30% dropout buffer is taken into account. The final sample size calculation amounts to 2400 patients with a reduction of 360 referrals.

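### The primary Poisson model uses KV bills counted during the intervention as its offset, so it tests referrals per bill with a denominator the intervention could change, while the stated outcome is the number of referrals

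*Protocol article*

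**What the plan says.** The Outcomes section defines the endpoint as a count: "The primary outcome measure is the number of conventional referrals from GPs to dermatologists". The Sample size calculation states the hypotheses on that scale: "The statistical null hypothesis is a reduction of 0%, the alternative is a reduction > 0" per cent. It plans on counts as well, since "48 dermatological referrals per year and GP practice are to be expected in the control population", to be set against 15% fewer.

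The Data analysis section then specifies a Poisson regression with study arm as a two-level factor and this offset: "To consider practice size and patient load, the number of practice KV bills during the intervention phase is applied as an offset". The same section repeats the timing when it argues that the offset will raise power, and it reports confidence intervals for each arm on the scale of referrals per KV bill.

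Two other places bear on whether bills could respond to the arm. The section on study design and setting says of ordinary KV work: "Within the regular contracts, the primary physician is remunerated per consultation and treatment". Table 2 lists, among the routine-data measures for both groups, "Ambulatory patient contacts with GPs and/or dermatologists due to skin conditions", including the billing keys.

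**The concern.** An offset enters the model with its coefficient fixed at one. The arm coefficient is then the log ratio of referrals per bill, and any difference between arms in bills passes in full into the estimate. That is harmless if bills cannot depend on the arm. Here they are counted while teledermatology is in use, and no level of the trial is blinded.

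The article gives some reason to think bills might move. Ordinary KV work is paid by consultation and treatment. Under the Intervention section, the practice takes photographs, creates the teleconsultation, receives the report and may resubmit the case. The protocol itself treats skin-related GP contacts as something to compare between groups.

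At stake are the meaning of the confirmatory test and the size of the reported reduction. The model could reject although referrals had not fallen, or it could hide part of a real fall. The stated purpose of the offset, practice size and patient load, does not require a denominator measured after randomisation.

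**Working it through.** **Inputs.** From the Sample size calculation: 36 analysable practices per arm, mean 48 referrals per practice-year, Poisson distribution, two-sided 5% level, 15% target reduction. From Data analysis: arm-only Poisson regression with log(bills) as offset. Not in the article: bills per practice and the effect of teledermatology on bills. I write x for the relative change in intervention-arm bills and treat it as an assumption.

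**The plan's own figures.** 36 × 48 = 1728, the article's patient figure (which it calls a total, although 36 is given per arm), and 15% of it is 259, given as 260. The 36 itself does not follow from the stated Poisson inputs: (1.96 + 0.84)² × 2 × 48 / 7.2² ≈ 14.5, or 15 per arm. That is a separate matter. I take 36 per arm as stated.

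**What the model tests.** With a single arm factor and an offset, the estimate is

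b = log(Y1/E1) − log(Y0/E0),

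where Y are total referrals and E total bills by arm. If expected referrals are equal and E1 = (1 + x)·E0, the expected value of b is −log(1 + x), not zero. The model's standard error is √(1/1728 + 1/1728) = √(2/1728) = 0.034.

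**Rejection with no change in referrals.** With d = log(1 + x)/0.034, two-sided rejection is Φ(−1.96 + d) + Φ(−1.96 − d).

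| x | d | Apparent reduction, 1 − 1/(1 + x) | Two-sided rejection |
|---|---|---|---|
| 0 | 0 | 0% | 5.0% |
| +1% | 0.29 | 1.0% | 6.0% |
| +2% | 0.58 | 2.0% | 9.0% |
| +2.3% | 0.67 | 2.2% | 10% |
| +5% | 1.43 | 4.8% | 30% |

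Simulation of the same model gives 6.0%, 8.9%, 10.3% and 30% for the four non-zero rows. A fall in bills shifts b by a similar amount the other way, so the excess rejections would then point to more referrals under teledermatology.

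**Effect on the estimate.** The per-bill rate ratio is the true ratio divided by (1 + x). With bills up 5%, a true reduction of 10.75% is reported as 15% (0.8925/1.05 = 0.85). With bills down 5%, a true reduction of 15% is reported as 10.5% (0.85/0.95 = 0.895).

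**Robust variance.** With between-practice variation (coefficient of variation 0.3, an assumption) and a robust standard error, simulated rejection is 5.3% at x = 0, 6.1% at +2% and 10.2% at +5%. The shift of −log(1 + x) in the estimate is the same.

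**With a pre-intervention offset.** E1 and E0 are fixed before the arm can act on them, so d = 0 and rejection stays at 5% whatever later happens to bills.

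**The case against.** The strongest objection is that the article never shows that x differs from zero. It does not define a KV bill, gives no bill counts and nowhere says that teledermatology adds bills. This stands, and it decides how strongly the point can be put.

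A reader might infer that the bias must favour teledermatology. The documents do not support that. The Background describes long waits for conventional referral and the Intervention section describes a report within 48 hours, so fewer interim GP contacts are as arguable as more.

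A reader might also try to size the rise: 48 candidates per practice, one to three extra bills each, over 2000 to 5200 bills a year, gives 48/5200 = 0.9% to 144/2000 = 7.2%. This range should not be relied on:
- The figure 5200 (about 1300 inhabitants per GP × 4 quarters) assumes one bill per patient per quarter, while the numerator counts one bill per contact. Under the quarterly definition, a patient already seen that quarter adds none.
- The figure 2000 has no source in the article.
- Every candidate is assumed to be teleconsulted, although GPs use the system only when unsure and patients may decline.
- Even at 5200 bills, +2.3% needs about 120 extra bills per practice (5200 × 0.023), or 2.5 per candidate.

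Nor does Table 2 make the outcome and the denominator the same quantity. It lists contacts for skin conditions, whereas the offset is all KV bills, so any overlap is partial. Study patients are also in the GP-centred contract, which adds a per-capita payment; that weakens the link from activity to bills without removing it.

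Finally, concurrent workload is a common exposure for a count over the same period, and a baseline count is less accurate where practices change size. That is a fair cost, but it does not make the concurrent count independent of the arm.

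**Conclusion.** The point holds as an avoidable vulnerability, not as a demonstrated bias. The article fixes an offset counted after randomisation, so the tested quantity is referrals per bill, while the outcome and null hypothesis concern the number of referrals. The two agree only if bills are unaffected by the arm, which the article does not state.

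The table's rejection rates are conditional on the assumed rise in bills, unchanged referrals, pure Poisson variance and 36 × 48 referrals per arm. The true size is unknown. It could be negligible, for example with one bill per patient per quarter or low uptake. The direction is also open. The change recommended is a cheap improvement.

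**What to change.** Define the offset as each practice's KV bills in the four quarters before the run-in phase, from the same source and by the same definition in both arms. Keep the model with concurrent bills as a sensitivity analysis, and report intervention-phase bills by arm so that readers can see whether they moved. State what counts as one KV bill.

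The cost is a sentence or two in the analysis plan and one earlier year of counts from the billing source already needed. The downside is a slightly less precise offset where practices grow or shrink between the two periods.

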## Methods

### Study design and setting

The study is planned as a cluster-randomized controlled confirmatory study, where a county is regarded as one cluster. The main scientific hypothesis is that the possibility of store-and-forward teledermatology in GP practices is going to reduce GP referrals to dermatologists by at least 15%. This protocol follows the Guidance of Standard Protocol Items: Recommendations for Interventional Trials (SPIRIT) 2013 Statement [22]. It includes the schedule of enrolment and relevant assessments (Fig. 1) using the SPIRIT figure template. A SPIRIT checklist is provided in Additional file 1.

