The federal state of Baden-Württemberg is one of Germany’s larger states with about 10 million inhabitants. It is organized into several *Landkreise* (counties) with variable population density, ranging from 3008 inhabitants per km^2^ in the urban region of Stuttgart to 101 inhabitants per km^2^ in the rural Main-Tauber County [25]. Likewise, the number of dermatologists per inhabitant varies from one statutory health insurance (SHI) dermatologist per 9617 inhabitants (City of Karlsruhe) to one dermatologist per 130,772 inhabitants (Sigmaringen County) [26]. The SHI GP-to-inhabitant ratio shows less variation: there is between one GP per 1070 inhabitants (Main-Tauber County) and one GP per 1501 inhabitants (Tuttlingen County) [26].

Eight counties were included in the study. Selection criteria for the counties were the closeness to the study center (Tübingen) and their similarity in study-relevant indicators (see Table 1). These parameters will be used for the counties’ matching and randomization process. Allocation of patients to control or intervention groups (−t_2_ in Fig. 1) is based on this randomization.

**Table 1 Tab1:** Matching parameters of the eight study counties in the federal state of Baden-Württemberg

County	Inhabitants per km^2^	Inhabitants	Dermatologist:inhabitant ratio	GP:inhabitant ratio
Böblingen	617	381,281	1:25,419	1:1352
Calw	195	155,359	1:51,786	1:1387
Esslingen	817	524,127	1:29,118	1:1368
Freudenstadt	133	116,233	1:58,117	1:1471
Reutlingen	274	282,113	1:18,808	1:1190
Rottweil	179	137,500	1:27,500	1:1127
Tuttlingen	186	136,606	1:27,321	1:1501
Zollernalbkreis	206	188,595	1:31,433	1:1266

*GP* general practitioner

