**Fig. 2 Fig2:**
[figure not shown]
Project timeline of the 3-year project. GP general practitioner

The cluster level “county” is randomized into four intervention and four control counties. In the intervention counties, data from non-participating HzV practices will serve as an internal control group at the cluster level “practice”. At the cluster level “patient”, data from nonparticipating patients are used as a second internal control group. No blinding is applied to any level of the trial. Figure 3 shows both study arms and an overview of the different cluster levels.

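### Counties are randomised four against four, but the primary Poisson regression treats GP practices as independent, so its p-value and confidence intervals are too optimistic unless referral rates do not vary between counties

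*Protocol article*

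**What the plan says.** The protocol article's section Study design and setting describes a "cluster-randomized controlled confirmatory study, where a county is regarded as one cluster". Under Study design, the county level "is randomized into four intervention and four control counties". The setting text states "Eight counties were included in the study" and, of the county indicators in Table 1, "These parameters will be used for the counties’ matching and randomization process". It does not give the pairs.

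Under Data analysis, "For the primary outcome, Poisson regression is chosen as an analysis tool". For practice size, "the number of practice KV bills during the intervention phase is applied as an offset". Study arm is the only factor named, and "The GPs are the unit of observation". No county term, random effect, robust variance or county-based degrees of freedom is mentioned for this model.

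The next paragraph of the same section promises generalized estimating equations for secondary outcomes. For GP-team analyses it says that "appropriate regression models without cluster adjustment are used, because the outcome is only measured once per GP team", and it singles out the teleconsultation-system data and the AOK insurance data. The sample size section contains no intracluster correlation, design effect or between-county variance.

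**The concern.** The reason given for leaving out cluster adjustment answers a different question. One value per practice means there are no repeated measures within a practice. It says nothing about whether practices in the same county resemble each other. They share the local supply of dermatologists, and they share the allocation. The randomised units number eight, but the model behaves as if there were about 72 independent ones.

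The trial is called confirmatory at a two-sided 5% level. If referral rates differ between counties for reasons unrelated to teledermatology, part of that difference falls into the arm contrast, and the planned standard error does not include it. The consequences are a false-positive rate above 5% and confidence intervals that are too short. The billing offset corrects for practice volume, not for county differences in referrals per bill. A fixed county effect cannot be added as a remedy, because each county lies wholly within one arm.

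**Working it through.** **Inputs from the protocol** (Sample size calculation, Study design): 48 referrals per practice-year; 15% reduction, so 48 × 0.15 = 7.2; Poisson counts; 36 analysable teams per arm; two-sided 5%; 80% power; 4 counties per arm. Spread evenly, that is 36/4 = 9 practices and 9 × 48 = 432 referrals per county.

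**Input not in the protocol:** k, the between-county coefficient of variation of the true referral rate. It is varied as an assumption.

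**The plan's own figure.** For a two-sample comparison with SD √48 = 6.93, n per arm = 2 × (1.960 + 0.842)² × 48 / 7.2² = 14.5, so 15 (16 with the exact t distribution). The stated 36 does not follow from the stated inputs; 36 per arm would give about 99% power. Reaching 36 at 80% power needs an SD of about 10.8, that is a variance about 2.4 times Poisson. Some practice-level overdispersion may be hidden in the figure, but no county component is stated. Also, 36 × 48 = 1728 is one arm's total, although the text calls it the overall total. Both readings are therefore carried below.

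**Type I error of the planned test.** Under no effect:

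- Variance of the log rate ratio that the model uses: 2/1728 = 0.001157.
- Actual variance with county variation: 2/1728 + 2k²/4.
- Ratio of the two: VIF = 1 + 432k².
- Actual type I error: 2 × [1 − Φ(1.96/√VIF)].

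At k = 0.10, VIF = 1 + 432 × 0.01 = 5.32, √5.32 = 2.31, 1.96/2.31 = 0.85, and the error is 0.395.

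| k | VIF | SE too small by | 36 per arm, no gain from matching | 36 in total (216 per county) | 50 per arm (600 per county) |
|---|---|---|---|---|---|
| 0 | 1.00 | 1.0× | 5% | 5% | 5% |
| 0.05 | 2.08 | 1.4× | 17% | 11% | 22% |
| 0.10 | 5.32 | 2.3× | 40% | 27% | 46% |
| 0.15 | 10.72 | 3.3× | 55% | 42% | 61% |

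VIF and the SE factor refer to 36 per arm. If matching halved the county variance with 36 per arm, VIF = 1 + 432k²/2 = 1 + 216k². That is the same arithmetic as the 36-in-total column, so about 27% at k = 0.10.

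**Simulation** (20,000 trials per setting, 9 practices per county) gave 17%, 40% and 55% for the planned test at k = 0.05, 0.10 and 0.15. A t test on county log rates with 6 df stayed at about 5% throughout.

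**Adding practice-level overdispersion** (practice CV 17.5%, close to what 36 per arm implies): the plain Poisson test has 21% error even at k = 0, then 30% at k = 0.05 and 45% at k = 0.10. Correcting for overdispersion at practice level, without a county term, still leaves 10% and 20%.

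**Power for a 15% reduction with a county-based test** (36 per arm, pure Poisson within county, no gain from matching):

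| k | t test, 6 df | paired t test, 3 df |
|---|---|---|
| 0 | 96% | 85% |
| 0.05 | 77% | 59% |
| 0.10 | 41% | 30% |

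**The case against.** The strongest reply is that the inflation depends entirely on k, which the protocol does not report. At k = 0 with Poisson counts the planned test is valid. This stands, and the conclusion is conditional for that reason.

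A reader might infer from Table 1 that k must be large, because dermatologist supply runs from 1:18,808 to 1:58,117, a 58,117/18,808 = 3.1-fold range. The document does not support that step. The ratio counts dermatologists per inhabitant, not GP referrals per bill, and nothing converts one into the other. The counties were also chosen for similarity and are to be matched. If adjacent dermatologist ratios were paired (an illustration, since the pairs are not given), the within-pair ratios would be 1.35, 1.01, 1.08 and 1.12. Matching could thus reduce the relevant variance. The planned model does not use it, however, and halving the variance still leaves about 27% at k = 0.10.

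Strengths and limitations says that the internal control group lets cluster effects be examined. That may be informative, but it does not enter the primary model or its p-value.

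The sentence on omitting cluster adjustment stands in the paragraph on secondary outcomes. Even so, the primary endpoint is a GP-level count from the same routine data, and the primary model as written follows the same logic. Taking the GP as the unit of observation is not itself the error, since a county random intercept is compatible with it.

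A reader might also infer that the teleconsultation-system outcomes are wrongly analysed. Outcomes such as time to answer arise per teleconsultation, but one summary per team would fit the stated rule. They are collected in the intervention group only, and secondary tests are not strictly confirmatory. The point applies only where teleconsultations are analysed as separate rows.

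**Conclusion.** The point holds in conditional form. The document states that counties are randomised and that practices are analysed without any county component, for a reason that does not address correlation within counties. This is written text, not a detail left to an unseen analysis plan. Unless true referral rates do not vary between counties and counts are purely Poisson, the primary p-value and confidence intervals are too optimistic.

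The size rests on assumed k, equal practices spread evenly over counties, and the reading of the sample size. Even k = 0.05 more than doubles the nominal error in every reading shown (11% to 22%). It would go too far to say that the intervals are far too short as a matter of fact, or that 40% is the expected error rate, because the documents give no k. A confirmatory 5% claim should nevertheless not depend on k being zero.

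**What to change.** Base the primary test on the county, by one of two routes:

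- **Two-stage analysis:** one log referral rate per county, compared four against four by a t test with 6 df, or 3 df if analysed as matched pairs.
- **Count mixed model:** a county random intercept, an allowance for practice-level overdispersion, and small-sample degrees of freedom based on the number of counties.

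Do not use an uncorrected sandwich variance with 8 clusters. A permutation test over four matched pairs has 2⁴ = 16 allocations, so its two-sided p-value cannot fall below 2/16 = 0.125.

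Limit the rule on omitting cluster adjustment so that it does not exempt between-arm analyses of AOK data from county clustering. Cluster teleconsultation-system outcomes by practice only where they are analysed per teleconsultation.

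Restate the power with an assumed between-county variance and its range. The argument that the offset raises power above 80% concerns variation between practices and does not cover county variation.

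The cost is mainly wording, plus a county code available to the analysts. The real price is statistical. With 36 per arm, interval half-widths grow by (2.447/1.96) × √VIF, about 1.8-fold at k = 0.05 and 2.9-fold at k = 0.10. The stated power becomes less favourable, as shown in the working, and with eight counties more practices per county would help only in part.
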